## 6. DESCRIPTION OF THE EVALUATION

### 6.1. Evaluation Questions

In tandem with the program, we will conduct an impact evaluation to measure the effectiveness of the program. The primary objectives of the evaluation will be to answer the following questions:

1. What is the impact of integrating community-based MNCH and PMTCT services using CHWs in Shinyanga, Tanzania on:
  - a. The timing of ART initiation among HIV-infected pregnant and postpartum women;

- b. Retention of HIV-infected women in care 90 days postpartum; and
  - c. Adherence to ART at 90 days postpartum.
2. Is the impact of integrating community-based MNCH and PMTCT services on retention in care and adherence greater among women who had more contact with CHWs?
3. Is integration of community-based MNCH and PMTCT services acceptable and feasible for CHW, health facility staff, and pregnant and postpartum women, and are there potential spillover benefits on other maternal health outcomes?

[figure not shown]

## 6. 2 Impact and Process Indicators

### Impact Outcomes:

1. Timing of ART initiation: The timing of ART initiation among HIV-infected pregnant women according to gestational age (The number weeks since the first day of the last menstrual period (LMP)). We hypothesize that women in intervention communities will initiate ART earlier than women in comparison communities.
2. Retention in care: Whether an HIV-infected pregnant or postpartum woman on ART is still in care 90 days postpartum (binary 1/0). In Tanzania, postpartum women on ART are typically scheduled for clinical monitoring for their own health at 7, 28, and 42 days (6

week postnatal visit) and then every 30 days thereafter until transfer to the HIV clinic at 18 months. We define retention as a woman who attended her scheduled visit between 60-90 days postpartum.

3. Adherence: We will measure adherence with the medication possession ratio (MPR), the proportion of days when ART was prescribed and an individual is in possession of ART (determined with pharmacy dispensing data). MPR is associated with short-term virologic outcomes. We will determine the proportion of women with MPR  $\geq 95\%$  at 90 days postpartum (binary 1/0).

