## 2. PROBLEM STATEMENT

Globally, the number of children born with HIV-infection declined 35% during 2009-2012, a reduction partly attributable to antiretroviral (ARV) prophylaxis preventing 670,000 children from acquiring HIV infection in low- and middle-income countries during this period. However, despite this substantial achievement in PMTCT, there are still significant challenges facing the global effort to achieve UNAIDS' goal of "virtual elimination" of mother-to-child transmission (eMTCT) by 2015. To prevent transmission to their infants, HIV-positive pregnant women need to receive a series of services including antenatal care (ANC), HIV testing, disease staging, and ART or ARV prophylaxis. In addition, HIV-exposed infants should receive ARV prophylaxis, be tested for HIV infection, be exclusively breastfed for the first 6 months of life, and receive cotrimoxazole prophylaxis to prevent opportunistic infections. Although these services have been shown to reduce the risk of MTCT to <5% in breastfeeding populations and <2% in non-breastfeeding populations, in sub-Saharan Africa, 49% of HIV-infected pregnant women are lost between ANC registration and delivery and miss some or all of the essential PMTCT services. Consequently, only 57–70% percent of pregnant women living with HIV receive ART or ARV prophylaxis, one of the key steps of the cascade.

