## **7. METHODOLOGY**

### *7.1 Definition of Baseline and Endline Cohorts of HIV-Infected Pregnant Women*

We will retrospectively abstract data from routinely collected information in CHW logs and facility registries of patient medical information (see **Figure 1** for an overview of the impact and process outcomes). The research team will collect data from two 6-month cohorts (baseline and endline) of women who are 90 days postpartum to ensure that we can measure retention in care and adherence at 90 days postpartum (**Figure 4**):

- The baseline cohort will include HIV-infected women who were 90 days postpartum between July 1 and December 31, 2014; this corresponds to infants born between April 1 and September 30, 2014. These women are unexposed to the intervention.
- The endline cohort will include HIV-infected women who are 90 days postpartum between May 1 and October 31, 2015, corresponding to infants born between February 1 and July 31, 2015. These women will have been exposed to the intervention during the last 4-9 months of their pregnancy and during their entire 0-90 day postpartum period. This is a reasonable amount of exposure to the intervention given that, on average, women in Tanzania are 5.4 months pregnant at their first ANC visit when they have the initial opportunity to initiate ART.

**FIGURE 4.** Cohorts for Baseline and Endline Data Collection

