**Table 1.**

| Evaluation Question                     | Data Sources               | Outcome / Indicator(s)   |
|-----------------------------------------|----------------------------|--------------------------|
| 1. Impact of the intervention on:       |                            |                          |
| a. timing of ART initiation             | ART register
CTC2 cards | Timing of ART initiation |
| b. retention in care 90 days postpartum | ART register               | Numerator:HIV-Infected   |

|                                                          |                            |                                                                                                                               |
|----------------------------------------------------------|----------------------------|-------------------------------------------------------------------------------------------------------------------------------|
|                                                          | CTC2 cards
CHW register | women retained in care at 90 days postpartum
Denominator: HIV-infected pregnant women                                      |
| c. adherence to ART 90 days postpartum                   | Pharmacy logbook           | ART adherence (MPR)                                                                                                           |
| 2. Impact heterogeneity by intensity of exposure to CHWs | CHW logs                   | Number of CHW visits to individual women                                                                                      |
| 3. Acceptability and feasibility                         | ANC register               | ≥4 ANC visits
facility delivery
postnatal visit attendance
EID testing
Denominator: HIV-infected postpartum women |

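### The powered outcome, retention at 90 days postpartum, has two incompatible denominators; the sample size fits only the on-ART one, and cohort entry has no rule for unrecorded deliveries

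*Protocol*

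**What the plan says.** Protocol section 6.2 (Impact Outcomes) defines retention as "Whether an HIV-infected pregnant or postpartum woman on ART is still in care 90 days postpartum" and sets the event: "We define retention as a woman who attended her scheduled visit between 60-90 days postpartum". The population is women already on treatment.

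Table 1 (section 7.2) lists the same outcome with "Denominator: HIV-infected pregnant women". The evaluation question in section 6.1, repeated in 7.4, asks about "Retention of HIV-infected women in care 90 days postpartum". Neither has an ART condition.

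Section 6.4 powers the study on this outcome: 67% versus 80%, ICC 0.05, 15 communities per arm, 36 observations per community, 80% power. The 67% rests on a preliminary local analysis of women who had initiated ART, of whom more than 36% were lost within 100 days.

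Cohort membership is fixed in section 7.1 by time since delivery, and the endline window is translated there into a range of birth dates: "corresponding to infants born between February 1 and July 31, 2015". The baseline cohort is built the same way. Section 7.3 takes denominators from the ANC logs and then looks up CHW logs by identifier. No rule covers a registered woman whose delivery is not recorded.

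**The concern.** The protocol names two populations for the one outcome on which it is powered, so two analysts following different sections would report different results.

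The two versions also differ in kind. ART start lies downstream of randomisation: section 3 hypothesises that the programme raises demand for ART, and timing of initiation is itself a primary outcome. Restricting retention to women on ART therefore compares groups whose make-up the intervention may have changed.

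Cohort entry by birth date raises a related difficulty. Section 2 cites, for sub-Saharan Africa, that "49% of HIV-infected pregnant women are lost between ANC registration and delivery". A woman who leaves care before delivery may have no delivery date in facility records. If such women fall out of the cohort, and the intervention changes either pre-delivery loss or the recording of deliveries, the arms are no longer comparable. Facility delivery, postpartum attendance and infant testing are all listed in section 6.2 as possible spillover benefits, so arm-dependent recording is credible.

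**Working it through.** **1. Reproducing the plan's figure.** Inputs from section 6.4: p1 = 0.67, p2 = 0.80, ICC 0.05, 15 clusters per arm, 80% power. Two-sided alpha of 0.05 is assumed, since the protocol does not state it.

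- Uncorrected n per arm = [1.96√(2 × 0.735 × 0.265) + 0.842√(0.67 × 0.33 + 0.80 × 0.20)]² / 0.13² = 179.7.
- With continuity correction: (179.7/4) × [1 + √(1 + 4/(179.7 × 0.13))]² = 194.8, or 195.
- Design effect = 1 + (36 − 1) × 0.05 = 2.75.
- 195 × 2.75 = 536.25, or 537 per arm; 537/15 = 35.8, or 36 per community.

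The stated figure reproduces, read as per arm. There is no arithmetic error.

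**2. The same sample under the Table 1 denominator.** Effective n per arm = 15 × 36 / 2.75 = 196.4. Power = Φ{[d√196.4 − 1.96√(2p̄(1 − p̄))] / √(p1(1 − p1) + p2(1 − p2))}, without continuity correction. Assume that women who never start ART count as not retained and that uptake is equal in the two arms. Section 2 says nearly one quarter of pregnant women living with HIV in Tanzania receive no ARVs or ART; 76% uptake is taken from that, with a range of 60% to 90%.

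| ART uptake | Comparison | Intervention | Difference | Power |
|---|---|---|---|---|
| Starters only (6.2) | 67.0% | 80.0% | 13.0 points | 83% |
| 90% | 60.3% | 72.0% | 11.7 points | 69% |
| 76% | 50.9% | 60.8% | 9.9 points | 50% |
| 60% | 40.2% | 48.0% | 7.8 points | 34% |

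For the 76% row: 0.76 × 0.67 = 0.509, 0.76 × 0.80 = 0.608, d = 0.0988; (1.3845 − 1.3764)/0.699 = 0.012; Φ(0.012) = 0.50.

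**3. Conditioning on ART start.** Suppose uptake rises from 76% to 86%, the women who would have started anyway stay at 67%, and the added starters are retained at r. The on-ART difference is (0.76 × 0.67 + 0.10r)/0.86 − 0.67. The all-women difference is 0.10r.

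| r | On ART | All HIV-infected women |
|---|---|---|
| 50% | −2.0 points | +5.0 points |
| 67% | 0 | +6.7 points |
| 80% | +1.5 points | +8.0 points |

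If the women who would have started anyway also improve to 80% and r = 50%, the on-ART difference is (0.76 × 0.80 + 0.10 × 0.50)/0.86 − 0.67 = 9.5 points (power about 55%). The all-women difference is 0.658 − 0.509 = 14.9 points.

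**4. Dropping women lost before delivery.** Suppose pre-delivery loss falls from 49% (section 2) to 30% (assumed), those not lost in either arm are retained at 67%, and those newly kept to delivery at r. Excluding lost women gives (0.51 × 0.67 + 0.19r)/0.70 − 0.67 = −4.6, 0 or +3.5 points at r = 50%, 67% or 80%. Counting them as not retained gives 0.19r = +9.5, +12.7 or +15.2 points. If the intervention leaves pre-delivery loss unchanged, and exclusion and retention are otherwise equal in the two arms, both differences are zero.

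**The case against.** The strongest reply is that the direction and size of any bias rest on figures the protocol does not give. That stands. A reader might infer that newly recruited starters must pull the estimate the wrong way. They do so only under the on-ART denominator, and only if they are retained less well than the others. Section 3 makes that plausible through Malawi data on same-day starters but gives no local figure. Under Table 1 the added starters raise the estimate in every case computed.

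A reader might also infer that losing undelivered women destroys the randomised comparison. Section 7.1 does not say they are dropped. Exclusion that is equal across arms shifts the level of retention without biasing the difference, and the difference-in-difference analysis in section 7.4 would partly cancel stable record gaps. Nor does defaulter tracing in the intervention arm alone show that births are captured unequally: section 7.2 describes CHW logs in comparison villages too, covering women who do not use clinics. That rescue is partial. The clinic identifier is added to the log only at the start of the study, and comparison CHWs may not know HIV status.

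On adherence, a reader might infer that "the proportion of days when ART was prescribed and an individual is in possession of ART" ignores days after a woman disappears. Under lifelong ART those days can equally be read as prescribed but not possessed. The wording is ambiguous, not shown to be wrong.

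An analysis plan that is not at hand may settle the handling of missing delivery dates. It would not remove the contradiction between section 6.2 and Table 1, or the mismatch of Table 1 with section 6.4.

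**Conclusion.** The concern holds in this form. The protocol states two incompatible denominators for its powered outcome, and its sample size belongs to only one of them. With 76% uptake, unchanged by the intervention, the Table 1 version has a 9.9-point effect and about 50% power (34% to 69% for uptake of 60% to 90%). That loss is conditional: if the intervention also raises uptake, the all-women effect can be larger than planned, as the 14.9-point case shows.

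The on-ART version conditions on a post-randomisation event and can bias the comparison, towards no effect or harm if added starters are retained less well, and the other way if they are retained better. The two denominators can give opposite signs for the same truth. Cohort entry by birth date can bias the comparison if the intervention alters pre-delivery loss or the recording of deliveries; the documents establish the missing rule, not the bias.

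These results rest on assumed uptake, an assumed 10-point uptake gain, assumed retention of 50% to 80% in the marginal women, an assumed fall in pre-delivery loss to 30%, and two-sided alpha of 0.05.

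**What to change.** State one primary denominator, in the same words, in sections 6.1, 6.2, 6.4, 7.1, 7.3 and Table 1: all HIV-infected women in the ANC register whose delivery date, or expected date where no delivery is recorded, falls in the cohort window. Count a woman with no recorded visit at 60 to 90 days as not retained. Report retention among ART starters as secondary.

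Restate the power, or the detectable effect, with a comparison rate that belongs to this denominator.

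Name the source of LMP or gestational age for women who never start ART. Table 1 takes ART timing from the ART register and CTC2 cards, and the ANC register contents listed in section 7.2 do not mention LMP. As a clarification, state that the medication possession ratio counts days after the last pick-up, up to day 90, as not in possession.

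The cost is mostly wording, a date rule and a revised calculation. The downsides are real: expected dates carry some error, absolute retention will be lower, and the stated power becomes less favourable. Women who never register for ANC remain outside the denominator, and registration is itself something the programme could influence.

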#### Process Outcomes:

In addition to the impact outcomes, we have identified three process outcomes to ensure that we assess potential spillover benefits on other maternal and child health outcomes. Thus, as part of Evaluation Question #3, we will also collect data on the following three process outcomes in addition to acceptability and feasibility:

1.  $\geq 4$  ANC visits: the proportion of pregnant women attending the WHO recommended  $\geq 4$  ANC visits;
2. Facility delivery: the proportion of pregnant women who deliver in a health facility; and
3. Postpartum visit: the proportion of HIV-infected women who attend the 6-week postpartum visit.
4. Early infant HIV diagnosis (EID): the proportion of HIV-exposed infants who receive an HIV test at 6-8 weeks.

### 6.3 Evaluation Design

The impact evaluation will evaluate the effect of integrating community-based MNCH and PMTCT services using CHWs in Shinyanga, Tanzania. Using a cluster randomized design, we will allocate 30 villages to the treatment or comparison condition and measure the community-level outcomes at baseline (0 months) and endline (9 months) using routinely collected data from CHWs and health facilities. We will determine the impact of the intervention on the primary outcomes of ART initiation, retention in care, and adherence to ART (**Evaluation Question #1**). We will determine whether the effect of the intervention is stronger among women who received more visits from CHWs (**Evaluation Question #2**). Lastly, we will conduct a mixed methods process evaluation with the primary stakeholders, including but not limited to CHWs, clinic staff, and pregnant and postpartum women, to assess the intervention's: 1) acceptability; 2) feasibility; and 3) potential spillover benefits on other outcomes (**Evaluation Question #3**). If the data from the evaluation supports scale-up of the integrated strategy, we will use these data to refine the intervention protocols for wider adoption within Tanzania and elsewhere.

### 6.4 Sample Size and Power

In health facilities where there are  $< 50$  HIV-infected pregnant or postpartum women in the baseline or endline cohorts (determined with the ANC register), we will abstract data from the ART register on all women. At health facilities where there are  $\geq 50$  HIV-infected pregnant or postpartum women in the cohorts, we will abstract a predetermined sampling fraction such that 75% of women are sampled from cohorts with 50-100 women, 50% of women are sampled from cohorts with 100-200 women, etc. This approach will ensure that the sample size is adequate to detect a minimum increase in retention in care at 90 days postpartum.

We have powered the study for the outcome of retention in care 90 days postpartum. In our aforementioned preliminary analysis of pregnant women in Shinyanga, we found that more than

36% of HIV-infected pregnant women who initiated ART were lost within 100 days. Thus, we will conservatively assume that in the comparison communities, 67% of women will be retained in care at 90 days postpartum. For logistical and budgetary reasons, especially given the rapid nature of the impact evaluation, we have determined that we can reasonably study 15 intervention communities (a total of 30 CHW, 2 per village, and 15 RCH facilities) and 15 comparison communities.

If we assume an ICC of 0.05 and that the intervention will increase the proportion of women who are retained in care 90 days postpartum from 67% to 80% (detectable effect size of 13 percentage points, or 20%), we will require at least 36 observations per community, or 537 observations from the intervention and comparison groups, to have 80% power to reject the null hypothesis of no effect. Obtaining data from at least 36 HIV-infected women per facility is well within the normal volume of clients at RCH clinics, as many RCH clinics initiate an average of 11 HIV-infected women on ART/ARVs per month. With at least 6 intervention months in each community, we will ensure that we can easily meet this goal.

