### 7.3 Sampling and Data Collection

For many of the impact and process outcomes, we will use ANC logs to abstract data from the women who will comprise the denominator (e.g., proportion of women retained in care 90 days postpartum). Once we identify these women through the health records, we can use their medical ID to find CHW logs. The logs will provide us with further details of the services provided to each woman.

In some health facilities, electronic medical records will be available and we will not have to sample a subset of women. However, in others the records will be fully paper based and we will have to sample women for data abstraction. In health facilities where there are <50 HIV-infected pregnant or postpartum women in the baseline or endline cohorts (determined with the CHW log and ANC register), we will abstract data from the ART register on all women. At health facilities where there are ≥50 HIV-infected pregnant or postpartum women in the cohorts, we will abstract a predetermined sampling fraction such that 75% of women are sampled from cohorts with 50-100 women, 50% of women are sampled from cohorts with 100-200 women, etc. This approach will ensure that the sample size is adequate to detect a minimum increase in retention in care at 90 days postpartum. In facilities where data are manually abstracted from paper records, we will use Qualtrics Offline Surveys on Android tablets.

In facilities with 50 or more HIV-infected pregnant women in the baseline or endline cohorts, we will use a systematic random sampling procedure with a random start. Research assistants will select a number from a random number table and then select the woman in this position for the study. The research assistant will then sample every  $k$  eligible woman thereafter, where  $k$  is the sampling fraction, described above.

**7.4. Evaluation Question #1:** What is the impact of integrating community-based MNCH and PMTCT services using CHWs in Shinyanga, Tanzania on:

- a. The timing of ART initiation among HIV-infected pregnant and postpartum women;
- b. Retention of HIV-infected women in care 90 days postpartum; and
- c. Adherence to ART at 90 days postpartum.

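### Sections 6.4 and 7.3: the 67% control rate is not conservative against the pilot figure it is drawn from, 537 is a per-arm number worded as covering both groups, and the sampling interval k cannot be carried out as defined

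*Protocol*

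**What the plan says.** Section 6.4 powers the trial on retention in care at 90 days postpartum. It cites a preliminary analysis in the same region in which more than "36% of HIV-infected pregnant women who initiated ART were lost within 100 days". From this it concludes: "Thus, we will conservatively assume that in the comparison communities, 67% of women will be retained in care at 90 days postpartum".

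The other inputs are 15 intervention and 15 comparison communities, an intracluster correlation ("If we assume an ICC of 0.05") and a rise in retention "from 67% to 80% (detectable effect size of 13 percentage points, or 20" percent. The requirement is given as "at least 36 observations per community, or 537 observations from the intervention and comparison groups". The power claimed for that number is 80%. The significance level and sidedness are not stated there.

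Sections 6.4 and 7.3 give the sampling rule: all women where the cohort is below 50, 75% from cohorts of 50–100, 50% from cohorts of 100–200, and so on. Section 7.3 carries this out by systematic sampling of every k-th woman after a random start, where k "is the sampling fraction, described above".

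**The concern.** Three statements in the sample-size argument do not fit together.

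- **Control rate.** The 67% is presented as a cautious inference from the pilot loss, but the complement of that loss is below 64%. The assumption lies on the favourable side of its own source.
- **Total.** Thirty communities at 36 each make 1,080, not 537. Nothing in the sentence says that 537 applies to each group.
- **Interval.** A sampling interval is a whole number and the fraction is 0.75 or 0.50. Every 0.75th woman cannot be selected, so field staff would have to improvise.

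This section is the only justification for the sample size. A team that took 537 as the overall target would collect half of what the calculation needs. A team that rounded the interval could fall below 36 in mid-sized facilities.

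**Working it through.** **Inputs.** From section 6.4: 67% and 80%, ICC 0.05, 15 communities per arm, 36 per community, 80% power. Two-sided α = 0.05 is my assumption; it is supported by the exact reproduction below.

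**1. Reproducing the plan's figure**
- Per-arm n without clustering (pooled null variance): n = [1.96·√(2p̄(1−p̄)) + 0.842·√(p₁(1−p₁)+p₂(1−p₂))]² / d², with p₁ = 0.67, p₂ = 0.80, p̄ = 0.735, d = 0.13. This gives n = 179.7.
- Continuity correction: (n/4)·[1 + √(1 + 4/(n·d))]² = 194.8, rounded up to 195.
- Cluster size: 15m / [1 + (m−1)·0.05] = 195, so m = 195 × 0.95 / (15 − 195 × 0.05) = 185.25 / 5.25 = 35.3, rounded up to 36.
- Design effect at m = 36: 1 + 35 × 0.05 = 2.75. Then 195 × 2.75 = 536.25, rounded up to **537 per arm**.

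Both 36 and 537 are recovered. Other two-sided 80%-power variants do not give 537: without the correction, the pooled formula gives 427.5 per arm, the unpooled 410 and the arcsine 418. Power at 15 × 36 = 540 per arm is 80.3%.

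**2. The number 537 read as a total**
- 30 × 36 = 1,080, and 2 × 537 = 1,074.
- 537 / 30 = 17.9 per community. Design effect: 1 + 16.9 × 0.05 = 1.845. Effective n per arm: 268.5 / 1.845 = 145.5.
- Power for 67% against 80% is then 66% (67% at 18 per community), or 71% without the continuity correction.

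**3. The control rate**
- Pilot: more than 36% lost, so retained < 100 − 36 = 64%.
- Effective n per arm at 36 per community: 540 / 2.75 = 196.4. Continuity-corrected power:

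| Control | Held fixed | Intervention | Power |
|---|---|---|---|
| 67% | plan as stated | 80% | 80% |
| 64% | 13 points | 77% | 78% |
| 64% | 20% relative | 76.8% | 76% |
| 64% | 80% target | 80% | 93% |
| 60% (assumed) | 13 points | 73% | 75% |
| 55% (assumed) | 13 points | 68% | 72% |

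The stated 20% is itself rounded: 13/67 = 19.4%. For 64% to 77%, 208 per arm before clustering are needed, which is 208 × 0.95 / (15 − 10.4) = 43 per community.

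The time horizon also differs. Section 7.1 says "women in Tanzania are 5.4 months pregnant at their first ANC visit" on average. If ART starts then, 90 days postpartum falls about (9 − 5.4) × 30.4 + 90 ≈ 200 days after start, against the pilot's 100. This is a reason to look below 64%, but the protocol gives no retention figure at that horizon.

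**4. The sampling step**
- Stated fractions: 0.75 × 50 = 37.5 is the smallest yield in any sampled facility, and 0.50 × 100 = 50. Both exceed 36.
- With k = 0.75 the rule cannot be run, and no whole-number interval yields 75%. If staff rounded to every second woman, cohorts of 50 to 71 would give 25 to 35 (rounding down).
- At the section 6.4 volume of 11 per month, a six-month cohort has 66 women: 0.75 × 66 = 49.5 by the fraction, but 33 by every second woman.

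**The case against.** The strongest defence is that the calculation works. On its stated inputs it reproduces exactly, and the operative instruction, at least 36 per community, is right and agrees with 537 per arm. Abstraction follows facility-level fractions, so a missing word beside 537 need not change what is collected. That stands: the fault is in the reporting, and the 66–67% power arises only if someone works to 537 as the overall target.

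On the control rate, the direction of the effect depends on what is held fixed. With the 80% target kept, 67% is the harder case. That also stands, which is why the plan must say what it fixes. It does not make 67% follow from more than 36% lost.

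A reader might go further and treat 64% as a ceiling, or extrapolate the loss to 200 days and put control retention far lower. The documents do not support this. The pilot counts loss after ART start, whereas section 6.2 defines retention by attendance at a visit 60–90 days postpartum. Section 5 notes that women may disengage and re-engage. Section 3 cites 77% of Option B+ women on treatment at 12 months in Malawi, alongside less favourable later data. Any figure for 200 days rests on an assumed hazard, and on a national mean first visit standing in for the date of ART start.

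A reader might also infer that the sampling step cannot deliver 36 per community. The stated fractions refute that. The shortfall needs a rounding that the protocol does not prescribe, although its definition of k leaves staff to find some substitute.

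**Conclusion.** Three statements are wrong as written, and all are cheap to correct.

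- **Control rate.** 67% is at least 3 points more favourable than the pilot figure it is drawn from, so calling it conservative is unsupported. At 64% the effect on power is modest and runs either way: 78%, 76% or 93%, depending on what is held fixed. Results for rates below 64% are assumptions.
- **537.** It is a per-arm requirement; the total is about 1,080.
- **k.** As defined it cannot be carried out at 75%. One natural improvisation would leave 33 women at the protocol's own typical volume.

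It would be wrong to conclude that the trial lacks 80% power on its own inputs; it has 80.3% for a two-proportion comparison. All powers here refer to that single comparison, with two-sided α = 0.05 assumed. They are not powers for the difference-in-differences analysis in section 7.4. For the same reason, the calculation does not establish that 1,080 are needed in each of the baseline and endline cohorts.

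**What to change.** 1. In section 6.4, delete the word conservatively or justify 67% from a source that matches the outcome and its timing. Add a short power table at 36 per community for control rates at and below 64%. State whether the 13-point gain, the 20% relative gain or the 80% target is held fixed, and label rates below 64% as assumptions.
2. Write 537 per group, about 1,080 in total. State α and sidedness alongside.
3. In section 7.3, replace the every-k-th rule with a random draw of the stated fraction from the numbered list of eligible women.

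The cost is a few sentences and one table, and possibly a less favourable stated power. No women are added beyond the 36 per community already planned.
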